**Methods:**

The JUMPFOOD study is a double-blinded, two-armed randomized controlled trial, in which the effectiveness of oral supplementation of hydrolyzed collagen/vitamin C combined with PTLE compared to PTLE with placebo on pain and recovery of function in athletes with PT will be investigated. Seventy-six athletes aged 16–40 years, with symptoms of PT for at least 12 weeks, who play sports at least once a week will be included. All participants will receive education, advice with regard to load management and a PTLE program according to the Dutch guidelines for anterior knee pain. In addition, the intervention group will receive daily 10 g hydrolyzed collagen and 40 mg vitamin C supplementation for 24 weeks whereas the control group receives 10 g maltodextrin placebo supplementation. Measurements will take place at baseline and at 12 and 24 weeks’ follow-up. Primary outcome is the VISA-P score, which evaluates pain, function, and sports participation. For secondary outcome measures, data with regard to pain during functional tests, flexibility measurements, blood withdrawals, imaging characteristics of the tendon, and health questionnaires will be collected. During the follow-up period, participants will register sports participation, amount of training and tendon load, pain during sports, co-medication, and side-effects in a digital weekly diary.

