#### Strategies to improve adherence to interventions {11c}

Before the start of the intervention, participants will receive an elaborative explanation about the supplement and the exercise program. The explanation is also provided on the website, including short video clips with the exercises and a pdf containing all information about the exercise program.

Two factors will be monitored to keep track of study adherence: (1) compliance to the supplement intake (number of empty and unused supplement sachets brought by the participant and via the weekly questionnaire) and (2) compliance to the exercise program (total percentage of prescribed exercises performed (amount of load and number of series and repetitions will be monitored)). This will be asked on a weekly basis using a short online questionnaire. These questionnaires will be checked on a weekly basis. When the questionnaire is not filled out on the designated day, a reminder will be sent. With no response, a day later, participants will be called to remind them about the questionnaire.

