#### Other outcomes

##### Weekly logbooks

Data on compliance to the training program, mean pain score during the exercises, and sport-specific training load will be registered on a weekly basis. The questionnaire will be automatically sent weekly as a reminder. In this online questionnaire, we ask the number of training days that week and the number of matches that week. We ask which percentage of the prescribed repetitions the participant had accomplished and the precise amount of load and number of series and repetitions of the exercise program executed. The training load that will be obtained from this questionnaire is defined as the total duration of training and matches played per week (minutes) multiplied by the experienced intensity of training sessions and games using the modified Borg CR-10 Rate of Perceived Exertion (RPE) scale [43]. In addition, we ask the level of pain when performing the exercises, and we ask for reasons why the participant has not performed the prescribed exercises. Answering options are (1) lack of time, (2) pain, (3) preferring sports activities, (4) rest day, and (5) lack of motivation. We ask whether the participant has returned to their sports level or not; answering options are (1) not active in sports, (2) no return to sports, (3) returning to sport but not in desired sport, (4) returning to desired sport but not at the preinjury level, and (5) returning to preinjury level in the desired sport. We ask how satisfied the participant is with the exercise program; answering options are (1) excellent, (2) good, (3) moderate, and (4) poor.

At the end of the study, participants will be asked whether they knew which of the two supplements they received during the intervention period. The results of the weekly questionnaire are stored using a secure data collection site where data can be accessed, submitted, and modified.

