The primary study parameter will be the difference between intervention and placebo in the change in VISA-P score (0–100) over time. The primary outcome will first be analyzed with a linear mixed model. When the residuals of the model are not normally distributed, we will use a generalized linear mixed model instead. As independent variables, the treatment (supplement or placebo), time (time points of the measured variable) and time × treatment will be fixed factors, and the participant will be used as a random factor. Adjustments will be made for those baseline variables that are associated with the primary outcome (*p* < 0.10), using a multivariable analysis and a stepwise backward elimination strategy. Examples of potentially associated variables are baseline vitamin C and collagen amino acid intake, baseline P1NP concentrations, compliance to PTLE program, compliance to supplement use, and use of co-medication. Secondary study parameters will be reported quantitatively as well, in the most commonly used way. For the secondary study parameters, we will choose between the generalized linear mixed model and the linear mixed model in the same manner as for the primary outcome. Here, as independent variables, the treatment (supplement or placebo), time (time points of the measured variable), and time × treatment will be fixed factors, and the participant will be used as a random factor. The dependent variable is the secondary study parameter in question (with as important dependent variables/outcome measures: pain during a single leg decline squat, ultrasound imaging abnormalities, UTC findings, and tendon and muscle stiffness). The same stepwise backward elimination strategy will be used as mentioned above. For parameters that are categorical (dichotomous, nominal, or ordinal) a generalized linear mixed model will be used that is applicable for that specific secondary variable (for example a logistic mixed model for dichotomous parameters, and an ordinal mixed model for ordinal parameters). For these parameters, a similar strategy will be applied as described above.

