### Methods in analysis to handle protocol non-adherence and any statistical methods to handle missing data {20c}

Consistent with the CONSORT statement, an intention-to-treat analysis will be performed. In order to ensure the integrity of the randomization process and to offer an authentic assessment of the treatment outcomes, we will implement the intention-to-treat principle, analyzing the entire study population irrespective of their adherence to the treatment. We will carry out sensitivity analyses to assess the influence of missing values in the outcome parameter on the results. Then, we will decide on a strategy on how to handle the missing data if necessary. If data is missing “completely at random” (MCAR), we will perform multiple imputation to model the missing data within the intention-to-treat analysis, thus preserving the variability inherent in the outcome variables [44–46].

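### The primary model may adjust for compliance and co-medication, which arise after randomisation but are listed as baseline covariates

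*Protocol article*

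**What the plan says.** The protocol article's section on statistical methods ({20a}) defines the target: "The primary study parameter will be the difference between intervention and placebo in the change in VISA-P score (0–100) over time". The model is a linear mixed model with treatment, time and their interaction as fixed factors and participant as random factor; a generalized version is used if the residuals are not normal.

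The covariate rule follows: "Adjustments will be made for those baseline variables that are associated with the primary outcome", at p < 0.10, by backward elimination. The examples are baseline vitamin C and collagen amino acid intake and baseline P1NP, and then "compliance to PTLE program, compliance to supplement use, and use of co-medication". Only the first items carry the word baseline. The same elimination strategy is applied to the secondary outcomes.

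Section {20c} commits to intention to treat, "analyzing the entire study population irrespective of their adherence to the treatment".

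Other sections say when the three variables are measured:

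- **Supplement compliance** ({11c}): "number of empty and unused supplement sachets brought by the participant and via the weekly questionnaire".
- **Exercise compliance**, in the logbook section, which reads: "Data on compliance to the training program, mean pain score during the exercises, and sport-specific training load will be registered on a weekly basis". Section {11c} says of both kinds of compliance: "This will be asked on a weekly basis using a short online questionnaire".
- **Co-medication** (abstract, Methods): "During the follow-up period, participants will register sports participation, amount of training and tendon load, pain during sports, co-medication, and side-effects". Section {11d} also places it in the weekly diary.

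**The concern.** A covariate measured before treatment cannot be changed by treatment, so adjusting for it keeps the comparison that randomisation created. That protection is lost for a variable that arises afterwards, and there are two ways to go wrong.

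- **Mediation.** If the supplement reduces pain, and less pain changes how much a participant exercises or how often painkillers are taken, then adjustment removes part of the effect the trial is meant to measure.
- **Shared causes.** If something unmeasured, such as prognosis or motivation, drives both compliance and VISA-P, and treatment also shifts compliance, then adjustment produces a difference between arms that treatment did not cause.

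The selection rule makes this worse. Keeping variables because they are associated with the outcome favours those that follow symptoms. The adjusted contrast would then not be the effect of being assigned the supplement, although the protocol presents it as the primary intention-to-treat result.

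**Working it through.** **1. Timing against label.** Compliance with a supplement or an exercise programme has no value before that supplement or programme starts. The two compliance variables therefore cannot meet the rule's own condition of being baseline variables. Co-medication could in principle have a baseline value, but {20a} does not specify one, and the abstract and {11d} put its recording in the follow-up diary.

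**2. Dependence on symptoms.** Section {11d} allows pain medication from a VAS pain score of 7 lasting at least 24 h. The weekly logbook lists pain as a reason for missed exercises. VISA-P itself rates pain. Both links run through what the primary outcome measures.

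**3. The plan's own figure.** Inputs from {14}: difference 13, SD 19, power 80%, significance level 0.05 (two-sided reproduces the stated number). With 35 per arm the noncentrality is (13/19) × √(35/2) = 2.86 on 68 degrees of freedom, which gives power 80.6%. The stated total of 70 is reproduced. With 9% loss, 70/0.91 = 76.9, against 76 stated. Nothing here is disputed, and the fix does not change it.

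**4. When the form of entry matters.** Write the model for participant *i* at time *t* as

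Y_it = μ_t + δ_t·T_i + γ·X_i + u_i + e_it.

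In the change from week 0 to week 24, γ·X_i and u_i cancel and δ_24 − δ_0 is untouched. A covariate that is constant over time and entered as a main effect therefore leaves the treatment-by-time contrast alone in complete data. If the covariate varies over time, γ·(X_i,24 − X_i,0) remains. If it interacts with time, (γ_24 − γ_0)·X_i remains. In both cases the treatment contrast moves whenever treatment shifts the covariate.

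**5. Simulated trials in the mixed-model setting.** The strength of the links between covariate, treatment and outcome is assumed; the protocol gives none.

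| Setting | Unadjusted | Adjusted | Change |
|---|---|---|---|
| 38 per arm, 9% random dropout, constant main effect | 12.8 | 12.8 | none |
| Same, time-varying and symptom-driven | 12.8 | 11.3 | −1.5/12.8 = −12% |
| Same, covariate × time | 12.8 | 10.1 | −2.7/12.8 = −21% |
| 35 per arm, time-varying co-medication | 13.0 | 11.2 | −1.8/13.0 = −14% |
| 35 per arm, adherence allowed to adjust the change (correlation 0.32 with change) | 13.2 | 12.0 | −1.2/13.2 = −9% |

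**6. Range over assumptions.** This uses a simpler model of change: 38 per arm, SD 19, 4,000 trials per scenario, and a covariate with within-arm SD 1 that treatment shifts by *a*.

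*Mediator*, assumed to carry 8 points per SD, true total effect 13. Expected adjusted effect = 13 − 8a.

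| a | Formula | Simulated | Power unadjusted | Power adjusted |
|---|---|---|---|---|
| 0 | 13.0 | 13.0 | 84% | 89% |
| 0.3 | 10.6 | 10.4 | 83% | 73% |
| 0.5 | 9.0 | 9.0 | 84% | 58% |
| 0.8 | 6.6 | 6.6 | 85% | 33% |

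*Shared cause*: the covariate has no effect on the outcome but correlates 0.6 with an unmeasured factor worth 10 points per SD. The within-arm slope is 0.6 × 10 = 6, so the expected adjusted effect = true effect − 6a.

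| a | True effect | Formula | Simulated | Type I error, adjusted |
|---|---|---|---|---|
| 0 | 0 | 0 | −0.1 | 4.8% |
| 0.3 | 0 | −1.8 | −1.8 | 7.6% |
| 0.5 | 0 | −3.0 | −2.8 | 9.3% |
| 0.8 | 0 | −4.8 | −4.7 | 18% |
| −0.3 | 13 | 14.8 | 14.7 | – |
| −0.5 | 13 | 16.0 | 15.9 | – |
| −0.8 | 13 | 17.8 | 17.9 | – |

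The bias can go either way, and there is none when treatment does not shift the covariate.

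**The case against.** The strongest reply is that the plan states only treatment, time and their interaction as fixed factors. It mentions no time-varying covariate and no covariate × time term. On the plainest reading a compliance summary enters as a constant main effect, and step 4 shows that the primary contrast then survives. This also held with 9% random dropout: over 150 simulated trials per scenario, the week-24 interaction moved by about 0.02 points on average and 0.31 at most. That stands, and it means the biases in steps 5 and 6 are not the certain result of the plan. It does not clear the plan, because these data are collected weekly and {20a} does not exclude time-varying entry. Where constant entry is harmless, it also does nothing useful for the primary contrast.

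Other points have some weight:

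- Medication use is asked about at screening, and a questionnaire covering co-interventions is given at baseline ({13}, Questionnaires), so a baseline co-medication value may exist. This is right, but it does not help the two compliance variables.
- Section {20c} says who is analysed, and a covariate excludes nobody. The wording is not breached literally. The purpose is, because conditioning on adherence is not an analysis irrespective of adherence.
- The variables are only examples, and each must pass selection; read strictly, the word baseline would exclude compliance. An analyst who follows the named examples would still put it in.
- Under a blinded placebo, a treatment shift in supplement compliance is not obvious, and recovered participants move to maintenance exercises. So the direction of any bias is uncertain, which is itself a reason not to adjust.

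**Conclusion.** The concern holds and should be corrected before unblinding. Confidence is high that the covariate list is wrong as written: two of the named variables cannot be baseline variables, the third is not specified as one, and all three are recorded in follow-up and open to influence from symptoms.

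Confidence in the size is limited. With a constant main effect, the treatment-by-time estimate is essentially unchanged. With time-varying or covariate × time entry, a true effect near 13 points shrank by about 9% to 21% in the mixed-model settings tried. In the simpler model of change it fell to between 10.4 and 6.6 under mediation; under a shared cause, type I error reached 7.6% to 18%, or the effect was inflated to between 14.7 and 17.9. All these figures rest on assumed links, and none can be derived from the protocol. The same rule reaches every secondary outcome, so the problem is not confined to VISA-P.

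**What to change.** In {20a}, or in the SAP before the codes are broken:

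1. Remove compliance to the exercise programme, compliance to the supplement, and follow-up co-medication from the covariate list of the primary model and all secondary models.
2. State that covariates are restricted to values measured before the first dose. If a co-medication covariate is wanted, name the baseline value explicitly. For P1NP, name the sample drawn before the first intake, since a second one is drawn 1 h afterwards on the same test day.
3. Report adherence and co-medication by arm as descriptive results.
4. If an effect among adherers is of interest, make it a separate supplementary analysis with its own stated estimand, for example of complier type.

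The cost is about one sentence of text. No extra data are needed, and the sample size of 76 is unaffected.

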### Interim analyses {21b}

Not applicable, as this trial has no DMC, the duration of recruitment is manageable and there are no potentially serious outcomes.

### Methods for additional analyses (e.g., subgroup analyses) {20b}

At the moment, additional analyses are not foreseen; however, in the future, we might analyze the difference between different sports, the difference between proximal or distal injury on the tendon, and the difference between affected and unaffected tendons in tendon structure over time.

### Methods in analysis to handle protocol non-adherence and any statistical methods to handle missing data {20c}

Consistent with the CONSORT statement, an intention-to-treat analysis will be performed. In order to ensure the integrity of the randomization process and to offer an authentic assessment of the treatment outcomes, we will implement the intention-to-treat principle, analyzing the entire study population irrespective of their adherence to the treatment. We will carry out sensitivity analyses to assess the influence of missing values in the outcome parameter on the results. Then, we will decide on a strategy on how to handle the missing data if necessary. If data is missing “completely at random” (MCAR), we will perform multiple imputation to model the missing data within the intention-to-treat analysis, thus preserving the variability inherent in the outcome variables [44–46].

### Plans to give access to the full protocol, participant-level data, and statistical code {31c}

We plan to write at least one scientific paper about the results from the JUMPFOOD study. This will be published (if accepted) in a peer-reviewed journal. In this manner, we plan to share our findings with the world. In combination with the registration in the Clinical Trials register and this design paper, the full protocol is already publicly accessible. The anonymous datasets analyzed during the current study and the statistical codes will be available from the corresponding author upon reasonable request after finalizing the papers necessary for completing the doctoral degree of the corresponding author.

## Oversight and monitoring

### Composition of the coordinating center and trial steering committee {5d}

Principal Investigator:

Design and conduct of JUMPFOOD.

Preparation of protocol and revisions.

Preparation of investigators brochure (IB) and CRFs [Case Report Forms].

Organizing steering committee meetings.

Managing CTO [Clinical Trials Office].

Publication of study reports.

Steering committee (SC):

Design and agreement of final protocol.

Budget administration.

Executive researcher:

Design and conduct of JUMPFOOD.

Preparation of protocol and revisions.

Preparation of investigators brochure (IB) and CRFs [Case Report Forms].

Organizing and steering committee meetings (weekly).

Study planning.

Organization of test days.

Provide annual risk report to ethics committee (METC-OOST).

SUSAR [Serious unexpected suspected adverse events] reporting to METC-OOST.

Responsible for trial master file.

Organization of central serum sample collection.

Data manager.

Follow-up of participants.

Publication of study reports.

Randomization person:

Randomization.

Independent expert:

Answering questions related to study.

### Composition of the data monitoring committee, its role and reporting structure {21a}

Not applicable. A DMC is not needed in this study as risks are very low for the participants and it is a single-center study.

### Adverse event reporting and harms {22}

All adverse events reported spontaneously by the participant or observed by the investigator or his staff will be recorded. Although no serious adverse events are foreseen, these will be reported to the ethical committee within 7 days of first knowledge. All adverse events will be followed until they have abated, or until a stable situation has been reached. Depending on the event, follow-up may require additional tests or medical procedures as indicated, and/or referral to the general physician or a medical specialist. Serious adverse events need to be reported to the medical ethical committee till end of study within the Netherlands.

### Frequency and plans for auditing trial conduct {23}

Auditing trials are not conducted as this is a single-center study with low risk for the participants.

### Plans for communicating important protocol amendments to relevant parties (e.g., trial participants, ethical committees) {25}

When an amendment is wanted in the study protocol, this will be reported to the medical ethical committee (METC-OOST). Only after agreement from the METC will this amendment be definitive.

### Dissemination plans {31a}

We plan to publish at least one scientific paper about the results of the JUMPFOOD study. This will be submitted to a peer-reviewed Q1 sports medicine or sports nutrition journal. In this manner, we plan to share our findings with the world. The study results will be released to the participating physicians, referring physicians, participants, and the general medical community. Results will also be presented at (inter)national conferences and we strive to implement our findings in future treatment guidelines.

## Discussion

Despite the high prevalence of PT among athletes and its potential impact on sports participation, management of (patellar) tendinopathy remains challenging. Hydrolyzed collagen and vitamin C supplementation appears to have a promising effect on the recovery of (chronic) patellar tendinopathy in combination with exercise therapy. Positive effects of hydrolyzed collagen supplementation have been found on the recovery of Achilles tendinopathy and several studies suggest an increased collagen synthesis with hydrolyzed collagen supplementation [8, 9]. In addition, vitamin C might play a role in the final step, the crosslinking of the collagen molecule, showing its importance in tendon injury recovery [10]. However, to our knowledge, no RCT has been performed yet investigating the effect of hydrolyzed collagen and vitamin C supplementation on the recovery of patellar tendinopathy. While there are not many studies on nutrition and tendon health, this is the first RCT to study the effectiveness of hydrolyzed collagen/vitamin C supplementation in combination with the PTLE program on the recovery of patellar tendinopathy in athletes. This is also the first study with the PTLE program that takes into account the training and competition load of the athletes during the entire study period using a web-based log/app. The JUMPFOOD study is one of the largest RCTs on PT. Including two additional intervention arms to disentangle the separate effects of collagen and vitamin C would make the study design more robust, but this would require an unrealistically high sample size. In addition, researchers were forced to choose block randomization to have both placebo and intervention evenly distributed throughout the year. For example, in July and August, most athletes exercise less or differently compared to when all competitions start in September, influencing their experienced PT pain.

Another strength of the JUMPFOOD study is that it evaluates a variety of outcome measures of the patellar tendon, including imaging, functionality, stiffness, and pain, resulting in a better understanding of the effect of PTLE and collagen on injury and its recovery. In addition, the study is incorporated into usual care/Dutch guidelines which might facilitate implementation of the results. If supplementation of collagen and vitamin C appears to be effective, this treatment approach can be implemented in daily sports medicine practice to improve the treatment outcome of patients with PT. Overall, this study helps to better understand the role of collagen and vitamin C in addition to PTLE in the treatment of PT and leads us a step further in achieving better treatment results for this common and bothersome sports injury.

